#### Primary outcome

The primary comparison of interest is the between-groups difference in SPADI score at 24 months. The estimate for this difference will be derived from a constrained longitudinal data analysis model.^43^ This will be a linear mixed-effects model, featuring SPADI score at baseline, 3-, 6-, 12-, 18- and 24-months post-randomisation as the outcome, intervention group, timepoint, age and gender as fixed effects, and participant identifier and trial site as random effects. A series of group-by-time point interaction effects will be included as fixed effects, thereby making no assumptions about the shape of the SPADI score trajectory over time. The model will be constrained so that the baseline SPADI scores are equal between groups.^43^ The model will use maximum likelihood estimation, with an unstructured covariance matrix. The between-groups difference in SPADI score at 24 months will be extracted from this model as the primary outcome and reported with a 95% CI and p value.

#### Secondary outcomes

The between-group differences for total SPADI score at 3-, 6-, 12- and 18-months, and over 24 months will also be extracted from the primary analysis model as secondary outcomes. The other secondary continuous outcomes (eg, SPADI pain and function subscale scores, OSS) will be analysed using an identical mixed-effects model with the same covariates and covariance structure. While also a continuous secondary outcome, the EQ-5D-5L will exclusively be used in the health economic evaluation.

ROM and strength are collected at two timepoints (baseline and 24 months). The 24-month outcomes for these measures will be compared via a mixed-effects linear regression model with intervention group as the predictor variable, as well as age, gender and baseline value of the outcome, and site as a random effect.

The ordinal outcome of the global perceived effect outcome at 24 months will be analysed using mixed-effects ordinal logistic regression, adjusting for age, gender and baseline combined SPADI score, with site as a random effect. Time-to-event outcomes (time to revision/re-operation/death) will be explored by comparing restricted mean survival times between intervention groups. Safety outcomes (adverse event rate, complication rate and types of complication) will be summarised across all timepoints at which they are collected.

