### Outcomes

There is no consensus on the optimal outcome measures in shoulder arthroplasty, although Outcome Measures in Rheumatology Clinical Trials (OMERACT) has recommended four mandatory domains for trials of shoulder disorders: pain, function, global effect and adverse events.^13^ In choosing the primary outcome measure for this trial, we have followed the guidance of the Difference ELicitation in TriAls (DELTA) group and DELTA-2.^14^ The SPADI is very reliable, has low floor and ceiling effects, is valid for use in shoulder arthroplasty research and, as it is highly sensitive to change, it best enables us to answer the question of superiority of rTSR over aTSR in the two key domains identified by both the Patient and Public Involvement (PPI) group and OMERACT, namely pain and function.^15^ There is also a strong correlation between SPADI score and ROM.^16^ The Oxford Shoulder Score (OSS) is included as a secondary outcome to enable comparison of the trial population with the NJR dataset to explore external validity. The NJR has previously evidenced ceiling effects of the OSS in shoulder arthroplasty and lower responsiveness to change, making it unsuitable as the primary outcome instrument.^17^ NICE has recommended the primary outcome should be collected at 24 months post-surgery.^10^

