#### Secondary outcomes

Combined pain and disability score: measured via the combined SPADI score at 3, 6, 12 and 18 months, and over 24 months.Individual pain and disability scores: measured via the subscale scores of the SPADI at 3, 6, 12, 18 and 24 months, and over 24 months.Pain and function: measured via the OSS, which is a 12-item patient-reported outcome measure of shoulder pain and function with five response categories and overall scale ranging from 0 (worst) to 48 (best).^19^ The OSS will be collected at 3, 6, 12 and 24 months.Global perceived effect: patient opinion about the change in their shoulder since the start of the trial will be assessed at 24 months via the question “Compared with just before the operation for your shoulder replacement at the start of the study, how would you say that your shoulder is now?”. Responses will be on a 5-point Likert scale with the following options: much improved, improved, same, worse and much worse.^20^Health-related quality of life: measured at 3, 6, 12 and 24 months via the EQ-5D-5L, a validated measure of health-related quality of life in terms of five dimensions (mobility, ability to self-care, ability to undertake usual activities, pain and discomfort, anxiety and depression) each with five levels of severity.^21^ The EQ-5D-5L will be used to calculate quality-adjusted life years (QALYs) according to NICE best practice guidance at the time of the analysis.ROM: The range of shoulder flexion, abduction, internal and external rotation will be assessed by a suitably trained blinded assessor at 24 months using a hand-held goniometer following trial specific instructions and recorded as continuous measurements except for internal rotation that will be assessed according to the position of the thumb to the spine.^22^Strength of shoulder: Shoulder strength will be measured at 24 months using a spring balance as described for the Constant Murley Score by a suitably trained blinded assessor.^22^ This will be done for both shoulders and repeated three times and will only be completed if the arm can be elevated to 90 degrees (abduction). Neither strength nor ROM will be collected during the interim follow-up timepoints given the need for in-person measurements by a trained team member. Both ROM and strength measurements will be collected only at baseline and at 24 months.Complications: Expected complications related to the affected shoulder will be recorded and will include (but are not limited to) deep and superficial wound infection (using Centers for Disease Control and Prevention definition),^23^ re-hospitalisation, and implant, nerve and skin problems. These complications will be recorded at 3, 6, 12 and 24 months. Complications specific to the arthroplasty implant (ie, glenoid loosening (keeled and pegged), scapula notching and lucency of the humeral stem)^24^,^26^ will be reviewed by the local surgeon using post-operative radiographs (typically anteroposterior and axial views) and 2 year radiographs (typically anteroposterior and axial views) or the most recent radiographs if not available at 2 years. This assessment will be performed using routinely taken radiographs and where feasible by a local surgeon who did not operate on the participant. Depending on the availability of funding, these radiographs will be pseudonymised of personal data and collected for central review independent of the surgeons at the local hospital.Re-operations: An operation to correct the complications of a previous operation due to, for example, an infection or dislocation. Re-operations will be recorded at 3, 6, 12 and 24 months.Revision and mortality: Rates of implant revision and patient mortality over the 24-month follow-up will be collected from hospital and the NJR records to identify patients in whom revision was undertaken elsewhere or death that is not recorded in the hospital records. The NJR definition of a revision will be used, which is any operation where one or more components are added to, removed or modified in a joint replacement or if a Debridement And Implant Retention with or without modular exchange is performed.^27^Resource use: Data on healthcare resource use will be collected to inform the economic evaluation (eg, length of hospital stay, re-hospitalisation, physiotherapy). Data will also be recorded about use of private care, days lost to work and normal activities. These data will be collected from participants and hospital records at 3, 6, 12 and 24 months.

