### Sample size

The primary outcome is the total SPADI score at 24 months. As our trial compares two active treatments, we expect a relatively small difference in SPADI score between groups at 24 months, so our target difference between the rTSR and aTSR groups is eight points (the smallest published, validated difference classed as clinically important).^34^ We also conservatively assumed a group SD of 25 points, based on three non-randomised studies.^35^,^37^ We plan to use a linear mixed-effects model in the primary outcome analysis, but due to a paucity of data in the literature to inform our between-measurement correlations, we instead calculate the sample size estimate based on an ANCOVA (‘baseline-as-a-covariate’) model.

Assuming a baseline/24-month SPADI score correlation of 0.35,^38^ 182 participants per group (364 total) are required to give 90% power to detect a difference of at least eight points (SD 25) between aTSR and rTSR, and a 5% significance level. Allowing for 15% loss to follow-up at 24 months,^39^ we aim to randomise a total of 430 participants.

The OSS is our key secondary outcome measure allowing direct comparison of the trial population to those in the NJR in order to explore external validity of the trial sample. Assuming a between-group difference of 2.7 points on the OSS, an expected SD of 8.80, and a baseline correlation of 0.35, the sample size of 430 would achieve 87.5% power using a similar ANCOVA analysis method and the same underlying assumptions.

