### Data collection

Data will be collected from participants at baseline, 3-, 6-, 12-, 18- and 24-months post-randomisation. There will be a secondary outcome endpoint of 18-month follow-up to collect the SPADI only to try to help maintain trial engagement and reduce missing data of the primary outcome. Baseline data will be collected with participants at recruiting sites by a delegated member of staff, for example, research nurses. Follow-up data collection of the primary outcome and most secondary outcomes will be by postal questionnaire with supplemental telephone/video conference follow-up for non-responders or collected in clinic when attending at these timepoints as part of their routine care. Delegated research staff will also collect data from hospital records at 3, 6, 12 and 24 months. This includes a local assessment of routine post-operative radiographs and those routinely taken at 24 months (or earlier if not routinely available at this timepoint) to assess complications specific to the arthroplasty implant. Final follow-up data collection will include an outpatient clinic attendance at 24 months to assess shoulder ROM and strength by a blinded assessor. All reporting of data collection will be undertaken in line with the CONSORT statement.^12^

To minimise attrition, we will use multiple methods to maintain contact with participants, including full contact details (postal address, mobile phone number and email address if available). For postal data collections, two reminders will be sent to non-responding participants (at 2 and 4 weeks past the due date), with a final attempt to obtain data 6 weeks post-due date. Newsletters will be circulated to participants during the trial to keep them informed and engaged.^40^ Given that the 24-month follow-up clinic is not a routine appointment at all participating hospitals, all trial participants will receive a £20 gift voucher for attending the clinic and as a thank you for completing their follow-up questionnaires.

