#### Missing data

The primary analysis model assumes missing outcome data are missing at random (MAR) and uses full information maximum likelihood to implicitly handle missing outcome data. It is expected that other covariates included in the model, for example, gender, are unlikely to be missing. Therefore, as it is unlikely to have a large proportion of missingness in the analysis, multiple imputation will not be performed as part of the primary analysis. However, it is possible that participants who failed to complete their follow-ups will differ from those who did (for example, had worse pain/disability following surgery and therefore would have scored higher on the SPADI if they had completed the follow-up). This would suggest the data were missing not at random and represent a departure from the MAR assumption. Additional sensitivity analyses will be conducted using a pattern-mixture model to examine how sensitive the primary treatment effect estimate is to an assumption that (a) all of these missing observations (if present) are poor outcomes in the SPADI, and conversely that (b) all of these missing observations are beneficial outcomes in the SPADI, and thereby modelling ‘best case’ and ‘worst case’ scenarios for the primary outcome analysis.

While the results of this sensitivity analysis will not be directly comparable to the primary analysis model, it will be able to give an indication of how sensitive the estimate of the treatment effect is to departures from the MAR assumption in the primary outcome data.

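### The 24-month range-of-movement comparison uses clinic attenders only and ignores follow-up SPADI and OSS, so it can be biased if attendance, or its link with function, differs between arms

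*Protocol article*

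**What the plan says.** All references are to the protocol article.

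- **How ROM is measured.** Data collection: "Final follow-up data collection will include an outpatient clinic attendance at 24 months to assess shoulder ROM and strength by a blinded assessor". Outcomes, Secondary outcomes: "Neither strength nor ROM will be collected during the interim follow-up timepoints given the need for in-person measurements by a trained team member". ROM therefore has a baseline value and one follow-up value.
- **The visit.** Data collection: "Given that the 24-month follow-up clinic is not a routine appointment at all participating hospitals". The same sentence adds that "all trial participants will receive a £20 gift voucher for attending the clinic".
- **Other outcomes.** Data collection has SPADI and most secondary outcomes returned by post, with telephone or video contact for non-responders, or collected at routine clinic visits. A participant who misses the 24-month clinic can still have a 24-month SPADI and OSS.
- **The stated ROM model.** Statistical methods, Secondary outcomes: "The 24-month outcomes for these measures will be compared via a mixed-effects linear regression model with intervention group as the predictor variable". The other terms are age, gender, the baseline value and a random effect for site.
- **SPADI and ROM.** Outcomes: "There is also a strong correlation between SPADI score and ROM". No figure is given.
- **Missing data.** The Missing data section deals with the primary SPADI model: missing at random, handled by full-information likelihood, and "multiple imputation will not be performed as part of the primary analysis". Multiple imputation appears only under Cost-effectiveness analysis.

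**The concern.** A regression on a single follow-up value drops everyone without that value. It is valid if attendance is unrelated to 24-month ROM given group, age, gender, site and baseline ROM. The collected variables most likely to be related to both attendance and ROM are the follow-up function scores, and these are left out.

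The likelihood-based handling described for the primary outcome does not help here. In the SPADI model, interim scores carry information about a missing 24-month score. ROM has no interim scores.

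ROM is one of the outcomes on which the meta-analysis cited in Background and rationale found the implants to differ, chiefly in external rotation, while function scores did not differ. A ROM result that departs from the SPADI result is therefore plausible. Readers would want to know that it reflects the implants and not who came to the clinic.

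**Working it through.** **The plan's own figures.** None is stated for ROM. For SPADI, n per arm = 2(1.960 + 1.282)² × 25² × (1 − 0.35²) / 8² = 180.1, so 181, against the stated 182. Then 364/0.85 gives 429, against 430. The sizing is sound and does not bear on this point.

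**Inputs.** From Sample size: 430 randomised (215 per arm), and a target SPADI difference of 8/25 = 0.32 SD. Assumed, because the article gives no ROM SD, ROM effect, ROM–SPADI correlation or attendance rate:
- ROM–function correlation 0.6 (also 0.4 and 0.8);
- baseline to 24-month ROM correlation 0.35;
- attendance 70–85%;
- a logistic link between attendance and 24-month function, with the slope given per SD;
- where a true effect is assumed, 0.32 SD on both ROM and function.

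**Standard error in SD units.** √(2/(215 × attendance)) × √(1 − 0.35²).
- 85% attendance: √(2/182.75) × 0.937 = 0.098.
- 70% attendance: √(2/150.5) × 0.937 = 0.108.

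**Simulation.** 200,000 per arm, correlation 0.6, group coefficient adjusted for baseline ROM. Imputation is within arm, from baseline ROM and 24-month function.

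| Attendance mechanism | True effect | Full data | Attenders only | Imputed |
|---|---|---|---|---|
| Same in both arms, 80%, slope 1 | 0 | −0.002 | −0.004 | −0.003 |
| Same, 80%, slope 0.5 | 0.32 | 0.318 | 0.310 | 0.317 |
| Same, 80%, slope 1 | 0.32 | 0.326 | 0.303 | 0.324 |
| Rates differ, 70% v 80%, slope 1 | 0 | 0.002 | −0.039 | 0.002 |
| Rates differ, 70% v 85%, slope 1 | 0 | −0.005 | −0.069 | −0.006 |
| Equal 80%, slope 0 v 1 | 0 | −0.001 | 0.090 | −0.003 |

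**Reading the table.**
- Same mechanism, no effect: the bias is nil.
- Same mechanism, true effect: attenuation is (0.318 − 0.310)/0.318 = 2.5% to (0.326 − 0.303)/0.326 = 7%, or about 5%.
- Rates differ by arm: 0.002 + 0.039 = 0.041 SD, and 0.069 − 0.005 = 0.064 SD.
- Slope differs by arm: 0.090 + 0.001 = 0.091 SD.

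A separate run at correlation 0.6 and attendance of 76–88% gave 0.03–0.09 SD when the arms differ, which agrees. Correlations of 0.4 and 0.8 scale the result roughly in proportion: slope 0 v 1 gives an attenders-only estimate of 0.057 and 0.125 under no effect. If the slopes have opposite signs (−0.5 v 1), the estimate reaches 0.140 at correlation 0.6 and 0.199 at 0.8. That is an extreme case and is not used in the conclusion.

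**In degrees.** If the ROM SD were 25 degrees (an assumption), 0.03–0.09 SD is 0.75–2.25 degrees, against a standard error of about 0.10 × 25 = 2.5 degrees.

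**Limit of the remedy.** The imputed column assumes that 24-month function is known for every non-attender and that attendance depends on it. If half the non-attenders also lack the 24-month SPADI, imputation removes only about half of the bias.

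**The case against.** The best defence is that the article describes its analyses in brief and leaves the detail to a statistical analysis plan. Regression on observed values is conventional for a secondary outcome with one follow-up, and naming that regression does not rule out imputing first. The sentence declining imputation concerns the primary SPADI analysis only. This stands so far as silence about missing ROM is no finding. What remains is the model as stated, which on its own uses attenders only, when a better analysis can be built from data already collected.

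Second, participants and assessors are blinded to 24 months and a voucher is offered, so attendance that differs by arm is less likely. This stands as mitigation. It does not exclude the problem, because function and complications may themselves differ by implant.

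Third, the simulation draws attendance from SPADI and then imputes from SPADI, so near-complete recovery is built in. This also stands: the remedy is only as good as the link between attendance and observed scores.

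A reader might infer more than the documents support:
- **That the ROM comparison is biased.** Non-attendance linked to function is not enough for material bias; the arms must differ in attendance or in that link.
- **That at least 15% will lack ROM.** "Allowing for 15% loss to follow-up at 24 months" is a sample-size allowance for SPADI, not a floor on missing ROM. No clinic attendance rate is given.
- **That the protocol expects patients with worse outcomes to be missed.** Missing data raises this only as a possibility, and about questionnaire follow-up.
- **That global perceived effect shares the problem.** It is a question put to the participant, and nothing ties it to the clinic visit.

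**Conclusion.** The point holds in conditional form. The stated ROM regression rests on clinic attenders and leaves out follow-up scores that the article itself describes as strongly related to ROM. If attendance, or its link with function, differs between arms, the bias is about 0.03–0.09 SD, or 0.3 to 0.9 of a standard error. If the mechanism is common to both arms, the bias is nil under no effect and about a 5% attenuation otherwise. These sizes rest on an assumed correlation of 0.6 and attendance of 76–88%, neither of which the article supplies.

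This is a secondary outcome and the primary SPADI result is untouched, so the priority is low to moderate. The point is confined to ROM. Strength shares the visit and the regression, but its 90-degree elevation rule raises a separate question.

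**What to change.** In the analysis plan, for 24-month ROM:

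1. Pre-specify multiple imputation by arm, with baseline ROM, age, gender, site, and SPADI and OSS at every visit at which they are collected as predictors.
2. Fit the stated regression in each imputed data set and combine the results.
3. Report this beside the attenders-only result.
4. Tabulate 24-month clinic attendance by arm and by 24-month SPADI, so that readers can judge whether the arms differ.

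The cost is a short paragraph in the plan and some programming. No new data are needed, and chained-equation imputation is already planned for the economic evaluation. The analysis plan is to be agreed before data collection ends, so the change can still be pre-specified. The downside is reliance on the imputation model, with only partial recovery where the 24-month SPADI is also missing.

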### Statistical methods

Statistical analyses will be detailed in full in a Statistical Analysis Plan agreed by the independent DMEC prior to the end of data collection and are described in brief below.

Statistical analyses will be on an intention to treat (ITT) basis, with participants analysed in the groups to which they were randomised. Between-group treatment differences will be reported in the form of point estimates with 95% CIs and p values. Statistical significance will be declared at the 5% level, and analyses will be conducted in the latest available version of Stata or similar statistical software.

Baseline characteristics will be reported descriptively overall and by treatment group. Continuous data will be summarised as means, SD, medians and ranges as applicable, and categorical data as frequencies and percentages. All trial outcomes will be reported descriptively by group at all time points at which they were collected.

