### Cost-effectiveness analysis

A comprehensive economic evaluation will be conducted to assess the cost-effectiveness of rTSR compared with aTSR. First, a within-trial analysis over the trial’s 24-month time horizon will evaluate the short-term cost-effectiveness of the two surgical approaches. Second, a decision-analytic model is proposed to extrapolate results beyond the trial period and evaluate the longer-term cost-effectiveness, provided sufficient data inputs are available to support robust modelling.

The cost-effectiveness analysis will follow NICE Health Technology Evaluations: The Manual^46^ and Decision Modelling for Health Economic Evaluation.^47^ The primary analysis will be conducted from an NHS and personal social services perspective, with a 24-month time horizon. Healthcare resource use, including that associated with the original shoulder surgery, adverse events, revisions and post-operative rehabilitation, will be used alongside published national unit costs and other sources to estimate the costs associated with both surgical approaches.^48^ The EQ-5D-5L will be used with an area under the curve approach to estimate QALYs accrued during the trial.^21 49 50^

Regression analysis, adjusted for key covariates, will be used to estimate net costs and QALYs by TSR allocation on an ITT basis. These will be combined to calculate the incremental cost-effectiveness ratio (ICER), expressed as the cost per QALY gained. A non-parametric bootstrapping resampling technique will be used to explore uncertainty and estimate the probability that rTSR is cost-effective compared with aTSR at different willingness-to-pay thresholds.^51 52^

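### The plan restricts EQ-5D-5L to a 24-month QALY total with no score difference at any time point, and commits complications only to a summary without an effect estimate or interval

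*Protocol article*

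**What the plan says.** Under Outcomes, Secondary outcomes, the Protocol article defines quality of life as a repeated measure, "Health-related quality of life: measured at 3, 6, 12 and 24 months via the EQ-5D-5L". For complications of the affected shoulder it says "These complications will be recorded at 3, 6, 12 and 24 months". The Baseline data section adds a baseline EQ-5D-5L. The Outcomes section also cites a recommendation of "four mandatory domains for trials of shoulder disorders: pain, function, global effect and adverse events".

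Statistical methods opens with a general format rule: "Between-group treatment differences will be reported in the form of point estimates with 95% CIs and p values". The same section promises descriptive results by group for every outcome at every collection time, and leaves full detail to a statistical analysis plan.

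Statistical methods, Secondary outcomes, then treats the two outcomes differently from their neighbours. On quality of life: "While also a continuous secondary outcome, the EQ-5D-5L will exclusively be used in the health economic evaluation". On safety: "Safety outcomes (adverse event rate, complication rate and types of complication) will be summarised across all timepoints at which they are collected".

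The Cost-effectiveness analysis section gives the use that remains for EQ-5D-5L: "The EQ-5D-5L will be used with an area under the curve approach to estimate QALYs accrued during the trial", followed by "Regression analysis, adjusted for key covariates, will be used to estimate net costs and QALYs by TSR allocation on an ITT basis".

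**The concern.** EQ-5D-5L has the same collection schedule as the OSS (baseline, 3, 6, 12 and 24 months). The OSS goes into the constrained longitudinal model and EQ-5D-5L is taken out of it. The restriction is stated outright, so an analysis plan that follows it could not contain an EQ-5D-5L score contrast, even at 24 months, the primary time point.

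Complications stand beside outcomes that all have a named between-group method, yet the commitment for them is only to summarise. The Introduction uses differing complication profiles as background to the trial: glenoid loosening was more common with the anatomic implant, and scapular notching was seen only with the reverse implant. If the SPADI result is close, quality of life over time and complications will weigh in the choice between implants. Counts by arm do not by themselves show how large a difference the trial can exclude.

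**Working it through.** **Step 1. Planned analyses side by side** (Outcomes, Baseline data, Statistical methods and Cost-effectiveness analysis).

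| Secondary outcome | Collected (months; 0 = baseline) | Planned between-group analysis |
|---|---|---|
| SPADI total and subscales | 0, 3, 6, 12, 18, 24 | constrained longitudinal model |
| OSS | 0, 3, 6, 12, 24 | same model |
| EQ-5D-5L | 0, 3, 6, 12, 24 | none by time point; adjusted QALY regression over 24 months |
| Global perceived effect | 24 | mixed-effects ordinal logistic model |
| Range of movement, strength | 0, 24 | mixed-effects linear model |
| Revision, re-operation, death | over 24 months | restricted mean survival times compared |
| Complications | 3, 6, 12, 24 | summary; no effect measure named |

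EQ-5D-5L is the only repeated continuous score excluded from the model. Complications are the only listed clinical outcome with no named contrast.

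**Step 2. What the QALY total can hide.** The plan specifies an area under the curve. I assume the trapezoidal rule without discounting. Collection times in years are 0, 0.25, 0.5, 1 and 2. The weight on the between-arm utility difference at each time is half the span between its neighbours:

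- 3 months: (0.5 − 0)/2 = 0.25
- 6 months: (1 − 0.25)/2 = 0.375
- 12 months: (2 − 0.5)/2 = 0.75
- 24 months: (2 − 1)/2 = 0.5

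With equal baselines, QALY difference = 0.25·d3 + 0.375·d6 + 0.75·d12 + 0.5·d24.

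Suppose one arm is ahead by δ at 3 and 6 months and the arms are equal at 12 months. The QALY difference is then zero when 0.5·d24 = −(0.25 + 0.375)·δ, that is, d24 = −1.25δ. A null QALY result is therefore compatible with a 24-month difference larger than the early one and in the opposite direction. This shows that cancellation is possible; it does not predict it.

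**Step 3. Width of the missing complication interval.** The plan states no figure to reproduce here, and its sample-size figures are not in dispute. The number per arm is 430/2 = 215 randomised, or 364/2 = 182 after the planned 15% loss. The document gives no complication rate, so all risks below are assumptions.

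Equal risk p in both arms: half-width = 1.96 × √(2p(1 − p)/n). For p = 0.10 and n = 215 this is 1.96 × √(0.18/215) = 0.0567.

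| Assumed risk | Half-width, 215 per arm (points) | Half-width, 182 per arm (points) |
|---|---|---|
| 2% | 2.65 | 2.88 |
| 5% | 4.12 | 4.48 |
| 10% | 5.67 | 6.16 |
| 15% | 6.75 | 7.34 |
| 20% | 7.56 | 8.22 |

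Unequal risks, n = 215: interval = d ± 1.96 × √((p1q1 + p2q2)/215).

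- 10% v 5% (about 22 v 11 patients): 0.05 ± 1.96 × √((0.09 + 0.0475)/215) = 0.05 ± 0.0496, or 0.04 to 10.0 points.
- 12% v 8%: 0.04 ± 1.96 × √((0.1056 + 0.0736)/215) = 0.04 ± 0.0566, or −1.7 to 9.7 points.

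At 2% only about 4 patients per arm would have an event (0.02 × 215 = 4.3), so the normal approximation is rough there and an exact interval is preferable.

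**The case against.** A reader might infer that the trial will be unable to state any quality-of-life or safety difference between the implants. The documents do not support that. The QALY regression is an adjusted, intention-to-treat contrast by allocation, and bootstrapping is planned to explore uncertainty in the cost-effectiveness result. Revision, re-operation and death are compared by restricted mean survival time, and re-operation is defined as surgery to correct complications, so the complications that lead to surgery do enter a comparison. All outcomes are reported by group, so crude differences can be worked out.

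A reader might also infer that the general format rule is contradicted. That is too strong: the rule says how reported differences are to be presented, and does not promise one for every outcome.

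The best remaining defence is that the effect measure for complications belongs to the statistical analysis plan, and that limiting EQ-5D-5L to QALYs is a deliberate choice consistent across the article. The first part has force, and the complication limb is weaker for it. The second does not remove the point. The restriction is affirmative text, and it leaves an outcome defined at four follow-up times without a modelled difference at any of them.

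By-arm descriptive tables are only a partial substitute. Raw EQ-5D-5L means are unadjusted for baseline and rest on those who responded. Complication counts by visit may include the same patient more than once. Infection, nerve or skin problems, loosening, notching and stem lucency can all occur without re-operation or revision.

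**Conclusion.** The point holds as a modest and inexpensive improvement. It does not touch the primary analysis.

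- **EQ-5D-5L (firmer).** The present wording rules out a score difference at 3, 6, 12 and 24 months. The single QALY contrast can be null while the arms differ in opposite directions early and late. The cancellation example assumes trapezoidal, undiscounted QALYs and equal baselines.
- **Complications (weaker).** The article commits only to a summary of a listed secondary outcome, with no estimate or interval. The statistical analysis plan could still supply one under the general format rule. Under assumed equal risks of 2% to 20%, the interval would be roughly ±2.6 to ±7.6 points with 215 per arm, or ±2.9 to ±8.2 with 182. The range depends wholly on the assumed rates.

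**What to change.** 1. **EQ-5D-5L.** Delete *exclusively*. Keep the QALY analysis as planned, and also analyse the EQ-5D-5L utility at baseline, 3, 6, 12 and 24 months with the constrained longitudinal model already planned for the OSS. Report the between-group difference at each follow-up with its 95% CI, labelled supportive.
2. **Complications.** Replace the commitment to summarise with counts by arm plus a risk difference and 95% CI for the proportion of patients with at least one complication by 24 months, counting each patient once. Give individual complication types as counts with unadjusted intervals, exact where events are sparse. Adjusted estimates for each rare type are not worth attempting.

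Both changes use data already being collected and can be written into the statistical analysis plan, which the article says will be agreed before data collection ends. The cost is some wording, a few lines of code and a few more supportive estimates to interpret.
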